#### Planned statistical analyses

Step 1: we will study relationships between EF and brain data collected at baseline for all participants based on a priori hypotheses and also in an exploratory way, using repeated measures Analysis of Covariance (ANCOVA), general linear models (GLM), correlations, and regression analyses. Apart from verifying a priori hypotheses, an additional goal is to identify potential confounding factors affecting our main outcome: EF, and particularly WM performance. Those confounding factors include socio-economic status, extra-curricular activities, aerobic physical fitness, and sleep. Apart from studying the influence of these factors on the outcomes, they also allow nuisance factor control, which will allow to objectively evaluate the OC and VA impact on EF in the following steps.

Brain data will be pre-processed and analyzed using in-house script routines calling the last versions of the standard neuroimaging software pipelines (e.g. Statistical Parametric Mapping 12 (or later version if released; https://www.fil.ion.ucl.ac.uk/spm/). We will generate a population-specific brain template. Individual brains and activation maps will be normalized on this template, critical for the validity of longitudinal brain plasticity results [106].

Step 2: we will examine and compare the development in both experimental groups and the CG over time for the comprehensive set of EF and brain data separately (T0 vs. T1 vs. T2). We will use linear mixed models (LMMs) with the open source software R [107] to evaluate the longitudinal effects for all behavioral variables separately, comparing all three groups over two years. LMMs are flexible, powerful, statistical models that can consider several levels of clustering, continuous and qualitative explanatory variables, as well as unbalanced data (pertinent if attrition differs per group). For testing specific hypotheses, we will add specific brain data in those LMMs (f.i. WM associations with CEN functional connectivity).

Near transfer scores closely representing direct benefits from the art interventions on the trained domains (musicality: IMMA [86, 87], visuo-spatial aptitude: the cubes test [84], teacher’s judgements, ratings by independent judges; see Table 3) will be analyzed in the same way. The results allow evaluating individual learning and the effectiveness of the courses.

For the brain data we will use univariate and multivariate analysis methods. Individuals’ intensity of training, progress, demographic characteristics, physical aerobic fitness and appreciation of the courses will be considered.

Step 3: we will analyze all data in a multivariate data-driven thus exploratory way. Separately analyzing behavioral data and several kinds of brain imaging data, cross-sectionally and over time, provides extremely valuable information on these data. Additionally, combining diverse behavioral and multimodal brain MRI data within data-driven multivariate analyses may unravel hidden “covert” relationships [108, 109]. These advanced analyses will encompass two main axes. The 1^st^ axis will be concerned with group inferences, asking “what intervention-related changes can be observed on imaging data at the group level?”, while the 2^nd^ axis will be concerned with individual prediction: “Can imaging features predict behavioral outcomes at the individual level?” To this end, we will consider joint analyses of imaging data (structural connectivity, functional connectivity data considered together).

In the 1^st^ axis (group-level analysis), we will use two methods which have been used successfully on multimodal brain imaging data, each carrying different assumptions about linearity of relationships and distribution of variables: multimodal Independent Component Analysis (ICA) [108, 109] on the one hand, and Partial Least Squares (PLS) [110–112] on the other. We detail these methods below.

Joint, fusion, and linked ICA [113, 114] are variants of ICA that allow combining different types of data such as functional and structural neuroimaging data. These analyses could reveal joint changes in different imaging modalities (i.e. covariations in functional and structural connectivity measures) and allow to investigate differences between our three groups [108, 113].PLS is another powerful technique that can identify components of multivariate relationships between imaging and behavioral data [111, 115], notably PLS correlation models [111]. PLS and sparse PLS may reveal hidden relationships between battery tests and MRI measurements before and after the regimens (OC and VA) and show whether these relationships differ between the groups. Implementations of these approaches are publicly available in addition to several in-house extensions that allow using them in the most flexible way, including machine learning [74, 116].

In the 2^nd^ axis (individual prediction), we will attempt to predict the difference in behavioral outcomes (digit span, auditory/tonal, and visual WM) from the difference in connectomes^3^ between time points T0 and T2. The control group will allow discarding developmental connectivity differences that are not related to our interventions or not meaningful for predicting working memory. Here, we will leverage recent advances in graph-based machine learning, particularly graph neural networks (GNN). We will use each subject’s connectivity values (either in the whole brain, or in specific functional networks of interest (CEN, SN)) as input to train a GNN model to predict the behavioral scores. The scores can be predicted one by one, or jointly by using a multi-output network (see Fig. 1 for an overview of the analyses). To improve performance, we will use a technique called *transfer learning*, by pre-training the GNN model using related tasks and scores from other cohorts, and then fine-tune using our own data. The team of [name] successfully developed related transfer learning approaches on other datasets. Further, we will use our newly developed graph data augmentation technique^4^ to ensure that sample size is not an issue. Using a GNN model allows us to perform this analysis for both the structural and functional connectomes, where functional connectomes are obtained either from resting-state or from task-based connectivity.

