Finally, we will also employ the International Matrix Test [90], to assess speech in noise perception abilities, which are known to improve with musical training in children [43, 91]. Improvements in speech perception, especially in noisy environments, can significantly enhance school performance and everyday communication [43], thereby positively influencing daily life functioning and academic success.

To avoid order effects, the different tests in the behavioral battery are carried out in two distinct sequences, counterbalanced between the children in each group. The alternation of difficult and simple tasks is balanced in each sequence.

The detailed behavioral and MRI batteries are depicted in Tables 3 and 4.

**Table 3 Tab3:** Behavioral data collected at all time points. Total testing duration 2*60 minutes, without the fMRI tests and judgements/ratings. It comprises testing of all main EF components using mainly the WISC: Wechsler intelligence scale for children–5th Edition [89] and the KiTAP: Test of Attentional Performance for children [92]

COGNITIVE DOMAIN	FUNCTION	NAME OF THE TEST	BRIEF DESCRIPTION	REF.
Music abilities	Rhythm perception	Intermediate Measures of Music Audiation (IMMA)	Pattern comparison, judge if same or different in rhythm RIGHT button for identical patterns, LEFT for different patterns	[87, 88]
Visuo-spatial abilities	1. Visuo-spatial reasoning & praxis 2. Problem solving	Cubes test (WISC-V)	Arranging physical pictured cubes in specific patterns according to a design	[89]
Working memory (fMRI)	Auditory tonal working memory	Pattern comparison (inspired by IMMA)	Compare two 3-note sinus tone patterns 1. Low load condition (3 identical notes): RIGHT button for identical patterns, LEFT for different patterns 2. High load condition (3 different notes): RIGHT button for identical patterns, LEFT for different patterns	Adapted from [87, 88]
	Visual-spatial working memory	Visual n-back	6-case spatial matrix containing appealing monster figures - conditions: 0-back, 2-back Right button for matched n-back trial l, LEFT button for unmatched n-back trial	[93]
Memory Systems	Short-term memory	Digit Span Forward (WISC-V)	Repeating series of digit sequences of increasing length aloud	[89]
	Working memory: information manipulation	Digit Span Backward (WISC-V)	Repeating series of digit sequences of increasing length aloud backwards	[89]

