2. Visual n-back WM, adapted from [93]	1 EPI run [*≈09:30*]; voxel size: 2.5 mm isotropic; 51 slices; FOV: 210x210x127.5 mm; TR/TE: 1000/30 ms; multiband accelerator factor: 3
*Resting State brain activity (RS-fMRI)* Measures activity at rest and global functional connectivity of the brain (temporal correlations of activity between distant regions) [103]	1 EPI run [*08:30*]; voxel size: 2.5 mm isotropic; 51 slices; FOV: 210x210x127.5 mm; TR/TE: 1000/30 ms; multiband accelerator factor: 3

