**Fig. 1 Fig1:**
[figure not shown]
Data analysis overview This table summarizes steps and methods used to achieve our ultimate goal i.e., the prediction of the main behavioral outcome: working memory improvement and development (WM: working memory; ANCOVA: Analysis of Covariance; LME: linear mixed model equations; GLM: general linear model; MRI: magnetic resonance imaging; ICA: independent component analysis; ICAPs: innovation-driven co-activation patterns, PLS: partial least squares; GNN: graph neural networks)

Significance level will be strictly controlled using false discovery rate special techniques for multiple comparison correction for univariate and multivariate analyses involving behavioral, MRI and combined behavioral and MRI data [117].

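### The individual-prediction analysis relates changes over the same T0–T2 interval, so it can show concurrent association but not forecast working-memory improvement; pairing a task connectome with its own run's score adds a session artefact

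*Protocol article*

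**What the plan says.** The second axis of Step 3 (Planned statistical analyses) is headed individual prediction. Its target and predictor are given in one sentence: the team will "predict the difference in behavioral outcomes (digit span, auditory/tonal, and visual WM) from the difference in connectomes", and the interval follows, "from the difference in connectomes^3^ between time points T0 and T2". The model is a graph neural network applied to structural and functional connectomes, and "functional connectomes are obtained either from resting-state or from task-based connectivity". The Fig. 1 caption describes the steps as leading to "our ultimate goal i.e., the prediction of the main behavioral outcome: working memory improvement and development".

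Table 3 places the tonal pattern-comparison task and the visual n-back under the domain "Working memory (fMRI"), so two of the three target scores are earned in the scanner. Table 4 gives each task a single EPI run of about 9 minutes 30 seconds, the second listed as "2. Visual n-back WM, adapted from [93"]. The digit span tests, such as "Digit Span Backward (WISC-V"), sit in a separate domain of Table 3. Study procedures with timelines lists the behavioral battery (two sessions on different days) separately from the MRI battery.

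Step 3 is labelled exploratory. The related secondary endpoint is worded as correlations between brain plasticity and EF performance change, not as prediction.

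**The concern.** Two separate problems arise.

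The first is timing, and it affects all three targets. A T0–T2 connectome difference is available only after the T2 scan, when the WM gain has already occurred. A good fit then says that brain and behaviour changed together. It does not say that an earlier brain measure tells us which child will improve. The T1 scan, which could put predictor before outcome, is not used in this model as described.

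The second is shared measurement, and it affects only some pairings. If the functional connectome comes from a WM task run and the target is the score from that same run, anything peculiar to the child in those minutes enters both sides. A restless or disengaged child may show altered connectivity and a poorer score without any lasting link between the two.

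The stated safeguards do not reach this second problem. The control group can help with average development, but session state varies within each child and is present in every arm. False discovery rate control deals with multiplicity. Testing on held-out children would not expose it either, because the shared variance is real covariance and would recur in them.

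At stake is the reading of a positive result. The protocol hopes its models will shed light on the brain mechanisms behind far transfer, and same-run covariance could be mistaken for such a mechanism.

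**Working it through.** The plan states no figure for this analysis, so there is none to reproduce. The sample used below follows from the plan: 50 × 0.70 = 35 per group, and 3 × 35 = 105 at T2.

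**Step 1: which pairings share a run.** There are three scores (digit span, tonal WM, visual WM) and four possible connectome sources (structural, resting-state, tonal-task run, visual-task run), counting each task run as its own source. That gives 3 × 4 = 12 pairings:
- 2 share a run (tonal score with tonal-run connectome, visual score with visual-run connectome);
- 6 share at most the MRI visit (each in-scanner score with its three other sources);
- 4 involve digit span, from the separately listed behavioral battery.

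**Step 2: what session state does to a change-on-change correlation.** Assume no lasting brain–WM link. At visit t let

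- X_t = trait_X + √s·S_t + √(1−s)·noise (one scalar connectome feature),
- Y_t = trait_Y + √s·S_t + √(1−s)·noise (the score from the same run),

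with independent traits, S_t the state of that session, and s the share of within-session variance due to it. All components have unit variance. Traits cancel in the T2−T0 differences, so

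- Var(ΔX) = Var(ΔY) = 2s + 2(1−s) = 2,
- Cov(ΔX, ΔY) = 2s,
- r = 2s/2 = s.

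With the shares expressed on total variance, r = state/(1 − trait). A split of 50% trait, 15% state and 35% noise gives 0.15/0.50 = 0.30. State 10–20% with trait 60–40% gives 0.10/0.60 = 0.17 to 0.20/0.40 = 0.50.

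**Step 3: how often this looks significant.** With Fisher's z, the expected statistic is atanh(r) × √(n−3). For r = 0.30 it is 0.3095 × √102 = 0.3095 × 10.10 = 3.13. The chance of exceeding 1.96 is Φ(3.13 − 1.96) = Φ(1.17) = 0.88. Simulation (4,000 runs, n = 105, nominal 5%) agrees:

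| Assumed s | Mean r | Rejections |
|---|---|---|
| 0 | 0.00 | 5% |
| 0.1 | 0.10 | 17% |
| 0.2 | 0.20 | 54% |
| 0.3 | 0.30 | 88% |
| 0.5 | 0.50 | 100% |

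**Step 4: the same check where state is not shared, or where time is ordered.**
- Score taken off the scanner on another day (the digit span case): mean r about 0, rejections near 5% at every s.
- T1 connectome given T0 connectome, against T2 WM given T0 and T1 WM: mean r −0.05 to 0, rejections 5–8%.
- T0 connectome and T0–T1 change together, against T2 WM given T0 and T1 WM: about 9% at s = 0.30 (2,000 runs).
- T0 connectome against T2 WM given T0 WM only: rejections up to 33% at s = 0.5, with a negative mean r (−0.15).

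The excess over 5% in the time-ordered models arises because earlier WM is measured with error that it shares with the earlier same-run scan. It disappears when the connectome does not come from the session in which the score was earned. Time ordering and exclusion of same-run pairings therefore belong together.

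**The case against.** A reader might infer that the whole axis measures only a shared-session association. The documents do not support that. Only 2 of the 12 pairings share a run, diffusion and resting-state data come from other sequences, and digit span is in a separately listed battery. T2 is a time point with several sessions, not one visit. The plan permits task-based connectomes but does not require pairing one with its own run's score. Its condensed form may leave motion handling and pairing rules to a fuller document.

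Prediction is also ordinary machine-learning language for estimating a score from features. On that reading the T0–T2 model does answer the question the axis poses, it fits the secondary endpoint on correlated changes, and Step 3 is openly exploratory. This stands. What it does not rescue is the Fig. 1 caption, which names improvement as the thing predicted and calls this the ultimate goal.

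A reader might also take the 88% rejection figure as the false-positive rate of the planned analysis. It is not. The state share is assumed and alone determines the result, and the calculation uses one scalar feature and a Pearson correlation, whereas the plan uses a graph neural network with transfer learning.

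Nor is T1 ignored throughout. Step 2 uses all three time points and may add brain data to the mixed models, and the secondary hypotheses say the Step 3 modelling takes all three into account. The gap is specific to the second axis.

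Finally, making a T0–T1 predictor the main model would have a real cost. The Background reports that group differences in the team's earlier trial were not yet significant after one year, and the review of far transfer argues that about two years are needed for important cognitive change. That is a good reason not to replace the T0–T2 model.

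**Conclusion.** The concern holds in limited form. The T0–T2 change-on-change model supports a statement about concurrent association, including estimation of a held-out child's score, but not one about forecasting WM improvement. This follows from the stated interval alone and applies to all three targets.

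The session artefact is confined to task-based connectomes paired with the tonal or visual score from their own run. It is weaker for structural, resting-state or other-run connectomes, and absent for digit span if that is tested on another day; the protocol lists the batteries separately without fixing the MRI day relative to the behavioral days. Its size cannot be read from the documents: the spurious r equals the assumed session-state share, 0 to 0.50 over the range examined, for one scalar feature at n = 105.

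This is an inexpensive improvement to an exploratory analysis. It does not bear on the group comparison of the primary endpoint.

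**What to change.** 1. Do not predict an in-scanner WM score from the connectome of the same run. Use structural, resting-state or other-run connectomes for the tonal and visual scores, or take digit span as the target.
2. Keep the T0–T2 change-on-change model, but report it as an association between concurrent changes, and align the Fig. 1 caption with that wording.
3. Add, alongside it and not in its place, a time-ordered model: T2 WM, given WM at T0 and T1, from the T0 connectome and the T0-to-T1 connectome change. Apply item 1 here too, so that the earlier scans do not share a run with the WM scores used for adjustment.

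All scans and scores are already planned, so the cost is wording and a little more analysis. The forward model sees only one year of brain change and may show a weaker association, so a null result from it should not be read as evidence against the two-year association.

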## Study objectives

### Hypotheses and outcomes

#### Primary hypothesis and expected outcomes

We anticipate cognitive far transfer effects following OC and, to a lesser degree following VA exhibited by improved EF performance, particularly auditory and visual WM performance during fMRI tasks, as compared to the CG. We expect greater improvement in OC except for visual WM.

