#### Secondary hypotheses and expected outcomes

We foresee that OC interventions will be associated with increased functional and structural brain plasticity as compared to VA and the CG (OC > VA > CG), notably in a set of temporal (medial and lateral (auditory)), prefrontal, and superior parietal areas, as well as in the basal ganglia (striatum), the cerebellum and the corpus callosum, supporting WM, EF and attention [24, 35, 73, 75].

We also anticipate greater Functional Connectivity (FC) changes following the same gradient (OC > VA > CG) in the Default Mode Network (DMN), Central Executive Network (CEN) and Salience Network (SN) [76, 77], in conjunction with increased or decreased structural connectivity [78]. In addition, plasticity associated with VA might occur specifically in the visual cortex.2)We hypothesize that we can model child EF development over two years in primary school children (initially 6-8 YOA) using multivariate data-driven analyses (see Statistical analysis plan and sample size calculation Planned statistical analyses, Step 3) that take into account all behavioral and brain data at all three time points, across the three experimental conditions (OC vs. VA vs. CG).

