## Statistics and methodology

### Statistical analysis plan and sample size calculation

The research statistician of the host institute of the principal investigator will assist with the behavioral analyses. Experts in MRI data analysis, machine learning, and multimodal data integration within the team will supervise both MRI data analysis and the combined multivariate analysis of behavioral and MRI data.

*Sample size*: We computed sample size separately for our main behavioral outcome (WM) and for fMRI and structural MRI data. Our sample size will consist of 50 children per group, and we account for an attrition of 30%, so for the final analyses, we will dispose of minimum 35 children per group.

For our main behavioral outcome WM: Based on our previous behavioral study on OC [1]: with an alpha=0.05 and power=0.80, the projected sample size needed to reach a similar effect size (GPower 3.1) *n*=48 is the total for a simple between-group comparison, thus *n*=24 per group.

For fMRI data: A cross-sectional study comparing visual working memory networks of two groups of 19 ADHD and 14 healthy children (8-12 YOA) using a similar design [104] obtained activation maps within groups and between groups with numerous clusters surviving to correction for multiple comparisons at *p*<0.05 FWE (family-wise error).

For structural MRI data: A study showed large developmental brain plasticity changes in gray/white matter volume and fractional anisotropy (FA) at the whole-brain level (*p*<0.05 corrected for multiple comparisons) using a longitudinal design in a group of 24 adolescents [105].

To address the issue of selective dropout, we adjusted our participant numbers to account for an anticipated attrition rate of 30%, while still meeting the necessary sample size criteria, computed above.

A longitudinal randomized controlled trial (RCT) with three measurement time points and sufficient sample sizes offers increased statistical power and helps mitigate the risk of false positive findings commonly associated with smaller, non-randomized studies.

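### The individual-prediction axis keeps connections that differ by arm and states no arm adjustment, so pooled accuracy can partly restate the group effect

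*Protocol article*

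**What the plan says.** The protocol article (Planned statistical analyses, Step 3) divides the exploratory multivariate work into a group-inference axis and an individual-prediction axis. The second asks: "Can imaging features predict behavioral outcomes at the individual level". For it, "we will attempt to predict the difference in behavioral outcomes (digit span, auditory/tonal, and visual WM) from the difference in connectomes" between T0 and T2, and the model uses each subject's "connectivity values (either in the whole brain, or in specific functional networks of interest (CEN, SN)) as input to train a GNN model". The control group's role on this axis is given in one sentence: "The control group will allow discarding developmental connectivity differences that are not related to our interventions or not meaningful for predicting working memory". No arm covariate, within-arm training or scoring, or arm-only benchmark is described for this axis.

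The hypotheses expect arm to move both sides of the prediction. On connectivity, Secondary hypotheses and expected outcomes says: "We also anticipate greater Functional Connectivity (FC) changes following the same gradient (OC > VA > CG"), for the default mode, central executive and salience networks. On WM, Primary hypothesis and expected outcomes expects gains in OC and, to a lesser degree, in VA compared with CG, and adds: "We expect greater improvement in OC except for visual WM".

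**The concern.** Arm is a common cause. If assignment raises WM change and also shifts connectivity change, the two correlate across children pooled from three arms, even when a child's connectome change says nothing about that child's WM change within any arm.

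The stated safeguard does not remove this. Discarding connectivity change unrelated to the interventions takes out maturation shared by all arms and leaves the connections that separate them. The second criterion, usefulness for predicting WM, does not help under pooling, because a connection that marks arm is then useful for predicting WM.

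At stake is the answer to the individual-level question. The Fig. 1 caption describes prediction of WM improvement and development as the ultimate goal, so a positive accuracy is likely to be read as a brain-behaviour link when part of it may be the Step 2 group comparison in another form.

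**Working it through.** **Inputs from the article**
- 50 children per arm and 30% attrition ("Our sample size will consist of 50 children per group, and we account for an attrition of 30" per cent): 50 × 0.70 = 35 per arm, 105 in total. The article's 35 is reproduced.
- WM sizing of 24 per group: "with an alpha=0.05 and power=0.80, the projected sample size needed to reach a similar effect size (GPower 3.1"). No effect size or sidedness is given. Solving the noncentral t for n = 24 and power 0.80 gives d = 0.826 two-sided or 0.729 one-sided.
- A small-effect case: Hedges' g = 0.26, from the meta-analysis of instrumental training cited in the Background.

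**Assumptions**
- Arm means of WM change are 0, d/2 and d for CG, VA and OC, with within-arm SD 1.
- Connectivity shifts follow the same 0, 1/2, 1 gradient.
- The within-arm link between connectivity and WM change is zero.

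**Step 1: what the arm label alone can predict.** The variance of the arm means is d²/6, so R² = (d²/6)/(1 + d²/6) and r = √R². The chance of p < 0.05 at n = 105 is about Φ(atanh(r)·√102 − 1.96).

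| d | R² | r | chance of p < 0.05 |
|---|---|---|---|
| 0.82 | 0.6724/6 = 0.112; 0.112/1.112 = 0.10 | 0.32 | 91% |
| 0.73 | 0.08 | 0.29 | 84% |
| 0.50 | 0.04 | 0.20 | 53% |
| 0.26 | 0.011 | 0.11 | 19% |

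This is the ceiling, reached only if the connectome identifies arm perfectly.

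**Step 2: one imperfect connectivity composite.** With arm shift s in the composite, r = (s·d/6)/√[(1 + s²/6)(1 + d²/6)]. At d = 0.83:
- s = 0.83: 0.1148/1.1148 = 0.10, which the formula above turns into about 18%.
- s = 1.5: 0.2075/1.238 = 0.17, about 40%.

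Simulation gave 18% and 41%. The arm-adjusted rate was about 5%.

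**Step 3: many connections, cross-validated.** The set-up was 3 × 35 children, 200 connections all carrying the shift, 5-fold cross-validated ridge and 500 runs per scenario. The critical r at n = 105 is 0.192 (two-sided 5%).

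| WM effect d | connectivity shift 0.3 / 0.5 / 0.8 SD: share of runs with r > 0.192 |
|---|---|
| 0.82 | 23% / 39% / 47% (mean r 0.08 / 0.15 / 0.17) |
| 0.50 | 11% / 15% / 19% |
| 0.26 | 5% / 8% / 8% |
| 0 | 4% / 5% / 4% |

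With no shift in the connections the share was 4-6% at every d. Sparser arm signals give less. With 400 connections, of which 10-25% were shifted by 0.5-0.83 SD, the share at d = 0.83 was 16-39%. Other settings gave 11-37% at 0.83 and only 5-8% at 0.5 or below.

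**Step 4: remove arm.** Scoring the same pooled predictions within arm gives 3-5% above 0.192, with mean r slightly negative (−0.02 to −0.06). Centring connectivity and WM on training-fold arm means gives mean r of about 0 and 7-9% above 0.192. That rate is already 7% with no arm effect at all, so it reflects dependence between folds and not arm. For the same reason, significance should come from permutation and not from a tabulated critical r.

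**The case against.** The strongest reply is that the point rests partly on silence. This is one paragraph of a condensed article, Fig. 1 is not shown, and scoring schemes and benchmarks are often left to a fuller plan. Pooling is nowhere explicit; the sentence on the control group could also fit training without that group or arm by arm. This stands as a limit: the finding is conditional on pooling. It does not dispose of the point, because the control-group rule is stated here and does not serve an individual-level question.

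A reader might infer that the model ignores age and baseline WM altogether. The article does not support that. Primary and secondary endpoints promises covariate control for age, gender, socioeconomic background and baseline WM, and Step 1 announces nuisance-factor control for the later steps. Arm is not among the factors named.

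A reader might also infer that all three WM targets follow OC > VA > CG. The OC advantage is explicitly not expected for visual WM, so the pattern there may differ.

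Arm is handled in the Step 2 mixed models, and the first-axis ICA and PLS analyses compare the groups, but these are separate analyses and do not adjust or score the network's predictions.

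Finally, prediction through arm is still prediction, and one secondary endpoint concerns brain-behaviour correlation following the interventions. That is fair, and it is why pooled accuracy should be kept as a description and not dropped.

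**Conclusion.** The concern holds in conditional form. If the arms are pooled and arm shifts both connectivity and WM as hypothesised, above-chance accuracy can partly restate the Step 2 group effect and does not by itself show an individual brain-behaviour link.

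The size rests on assumptions: the back-solved effect, the number and shift of the connections, ridge in place of the network, and a critical-r criterion that the article does not set. At an effect of about 0.83 SD roughly 10-45% of runs are above the critical value; at 0.5 SD between 5% and 19%; near 0.26 SD there is little inflation. It would therefore go too far to say that effective interventions make a false individual prediction certain, or that any positive accuracy is spurious.

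Step 3 is labelled exploratory and the primary group comparison is untouched. The change is worth making because it is nearly free and bears directly on how the axis will be interpreted.

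**What to change.** In Step 3, 2nd axis:
- State whether the arms are pooled for training and scoring.
- Report the gain in out-of-sample accuracy over a benchmark containing arm and the covariates already planned (age, gender, socioeconomic status, T0 WM), and/or accuracy within arm, with arm means estimated in the training folds. Test within-arm accuracy by permuting children within arm.
- Reword the control-group sentence so that intervention-related connections are identified from the between-arm contrast of T0-T2 change, inside the training folds only.
- Keep pooled accuracy as a descriptive figure that includes the intervention effect, and rest the individual-level conclusion on the arm-adjusted result.

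The cost is a few lines of wording and one benchmark model, with no new data. The drawback is that the arm-adjusted accuracy will be lower than the pooled figure.
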